### Intervention fidelity

A fidelity-monitoring tool has been developed by the CHAP research team in association with TRT group leaders in order to promote and monitor adherence to the core design of the programme. The fidelity-monitoring process will be implemented by TRT group leaders, who will share the data with CHAP for research purposes. After each TRT session, the group leaders complete a self-report adherence checklist, which captures group leader details; number of participants; use of interpreter(s); number of people who required the safety protocol; and the range of core components delivered. Session attendance lists will also be shared with CHAP to inform individual participant dose.

### Data collection

Pre-intervention data collection and randomisation is planned to take place between January 2019 and February 2021. End of TRT programme delivery data collection occurs about 8 weeks post pre-intervention data collection, and is therefore projected to take place between April 2019 and May 2021. Endpoint data collection occurs about 20 weeks after pre-intervention data collection and is projected to take place between July 2019 and September 2021.

Outcome data will be collected using a secure online platform (Qualtrics). TRT facilitators will be given the option of submitting fidelity data online or on paper forms. Data will be exported/inputted into an SPSS file for analysis. Anonymous participant identity numbers will be used. The file will be saved on the university server, which is automatically backed up. All procedures comply with current regulations on personal data management.

The youth (and legal guardian if the youth is < 15 years) will be informed that the data provided will be treated confidentially. He/she will be made aware that in published reports the results will be reported anonymously and at a group level, meaning that it will not be possible to identify any individual or attribute any information to them. Participants will be informed that if they disclose anything concerning their personal safety, then a safety protocol will be implemented.

### Statistical methods

Baseline and demographic characteristics will be summarised using means and standard deviations (or medians and interquartile ranges) for continuous variables and percentages for categorical variables. A set of strategies will be employed to minimise the amount of missing data (e.g. offering incentives for completing follow-ups). Reasons for dropouts for each condition will be reported. The possible impact of missing data will be examined via sensitivity analyses of augmented data sets. Including the dropouts and participants with missing data will be made possible by using modern analytical methods.

The comparison of the trial arms will use an intention-to-treat framework with participants analysed according to the trial arm to which they were randomised, regardless of whether or not they received the intervention. Linear mixed models will be used to compare outcomes for the trial arms. The primary outcome is total score group differences on the mental health outcome measures (i.e. CRIES-13, PHQ-9, GAD-7) after programme delivery (T2). The secondary outcomes are mental health outcome measures (i.e. CRIES-13, PHQ-9, GAD-7) total scores at endpoint (T3) and GSE and Cantril Ladder total scores after programme delivery and at endpoint (T2 and T3).

For the mental health outcome measures (CRIES-13, PHQ-9,; GAD-7), participants will also be classified as ‘recovered’, ‘improved’, ‘unchanged’ or ‘deteriorated’ based on the Reliable Change Index (RCI) and Clinically Significant Change (CSC) approach [10, 13]. This approach incorporates both a measure of whether the change in scores is larger than what is expected due to outcome measure reliability as well as the participant’s shift from a clinical state to a non-clinical state. The proportions of classifications will be compared across the trial arms.

Fidelity to the design of the intervention will be summarised using descriptive statistics. It will be assessed in terms of the different dimensions measured (adherence and dose). A secondary analysis will be undertaken to quantify the extent to which the intervention effect on the primary outcomes is determined by participation in the intervention (number of sessions received). Further moderation analyses will examine the associations between improvement status and participants’ characteristics (e.g. age, gender, suicidal ideation).

For the economic evaluation, the outcomes and costs between the intervention and control groups will be compared using generalised linear models (GLMs), which allows the consideration of other distributions and functional forms to fit the data [2]. Two types of evaluation will be conducted: (1) a cost-utility analysis with outcomes measured in QALYs and (2) a cost-effectiveness analysis with proportion of participants classed as treatment success expressed as incremental cost-effectiveness ratios [8]. The cost-effectiveness ratios describe (1) the price for one additional QALY, i.e. one life year with full health, and (2) the price to get an additional successfully treated participant.

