## Objectives

The objectives of the trial are:
To evaluate whether the TRT programme has a positive effect on unaccompanied refugee youth mental health in comparison to similar youth who only receive services as usualTo evaluate whether the TRT programme has a positive effect on unaccompanied refugee youth self-efficacy and well-being, which relate to the programme theory of changeTo identify which subgroups report the most/least benefit of TRTTo describe the extent to which TRT is implemented with fidelity to programme designTo estimate the cost-utility and cost-effectiveness of the TRT programme.

It is hypothesised that, when compared with youth who have not received the intervention (the waitlist-control arm), youth who have received TRT (the intervention arm) will demonstrate fewer self-reported symptoms of mental ill health, specifically PTSD, depression and anxiety symptoms. It is further hypothesised that, when compared with the waitlist-control arm, the intervention arm will report greater self-efficacy and well-being.

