### Sample size

Recruitment of 218 eligible youth to the project (109 per trial arm) will allow detection of an effect size of 0.5 at *p* < 0.05 with 80% power and allows for a study dropout rate of up to 41%, as informed by an exploratory study (an effect size of 0.5 requires a minimum sample size of 64 participants per trial arm).

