### Outcome measures

The study will primarily measure changes in youth self-reported mental health, specifically symptoms of PTSD, depression and anxiety. A combination of primary mental health measures is being used due to the complex trauma that can be experienced by the youth. Apart from adverse events before and during migration, the asylum and resettlement process per se involves stressors. Complex trauma can lead to social difficulties, behavioural and emotional symptoms, psychosomatic problems and sleep problems as well as PTSD symptoms [11, 22, 33].

Secondary assessments will include measures of self-efficacy and well-being, both of which relate to the TRT programme theory of change. All outcome measures will initially be available in Swedish, English, Arabic, Dari, Farsi, Somali and Tigrinya, with other languages made available if necessary. The measures will be administered pre-intervention (T1), after intervention delivery (T2) and a few months later (T3). The specific metrics, methods of aggregation and time points for the outcomes are described in the Statistical methods section.

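### Three measures share primary status at T2 with no stated success rule, while the 5% alpha and 80% power describe one unnamed comparison, so the two figures cannot both be assumed for the primary outcome

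*Protocol article*

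**What the plan says.** The Statistical methods section defines the primary outcome in one sentence: "The primary outcome is total score group differences on the mental health outcome measures (i.e. CRIES-13, PHQ-9, GAD-7) after programme delivery (T2"). Later in that section the same set appears in the plural, where a dose analysis asks how far "the intervention effect on the primary outcomes is determined by participation in the intervention".

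The Outcome measures section gives the reason for having several: "A combination of primary mental health measures is being used due to the complex trauma that can be experienced by the youth". It then refers the reader to Statistical methods for metrics, aggregation and time points. The hypothesis under Objectives covers all three domains, stating that treated youth "will demonstrate fewer self-reported symptoms of mental ill health, specifically PTSD, depression and anxiety symptoms". It does not say whether an effect on one domain would be enough.

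The Sample size section describes a single calculation, at p "< 0.05 with 80% power", and adds that "an effect size of 0.5 requires a minimum sample size of 64 participants per trial arm". It names no measure. The article states no test order, alpha split, adjustment or rule for combining the three results.

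**The concern.** The trial is sized for one test and declares three. What the stated 5% and 80% mean then depends on a rule that the article does not give. If a significant result on any one measure at 0.05 supports the claim, the chance of a false positive primary finding exceeds 5%. If all three must be significant, the chance of success under the planned effect is below 80%.

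A split result is foreseeable, for instance an effect on CRIES-13 but not on GAD-7, and the article gives no reading of it. Blinding cannot protect a later choice of lead measure: the Blinding section says that data collection is open and that allocation can be recognised in the outcome spreadsheets. Only a rule fixed in advance can do so.

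**Working it through.** **Inputs from the protocol.** Three measures at T2, none ranked (Statistical methods). Effect size d = 0.5, alpha 0.05, power 80%, 64 evaluable per arm, 41% dropout, 109 recruited per arm (Sample size). 1:1 allocation, superiority (Design). Sidedness is not stated.

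**Step 1: the plan's own figure.** The normal approximation is n per arm = 2(z₀.₉₇₅ + z₀.₈₀)²/d² = 2(1.960 + 0.842)²/0.25 = 62.8, so 63. The t-test version gives 63.77, so 64. A one-sided test would give 50, so the plan's figure is two-sided. Dropout: 64/(1 − 0.41) = 108.5, so 109 per arm and 218 in total. The figure reproduces for one two-sided comparison. Power at 64 per arm is 80.1% (t) or 80.7% (normal).

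**Step 2: three measures.** With 64 per arm the test statistic has mean 0.5 × √(64/2) = 2.83 under the planned effect. I assume d = 0.5 on all three measures and an equal correlation r between the test statistics. The article gives no correlation, so r from 0 to 0.9 is an assumed range.

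At r = 0 the results can be checked by hand:

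- Any of three at 0.05, no true effect: 1 − 0.95³ = 14.3%.
- All three at 0.05: 0.807³ = 53%.
- Each measure at 0.05/3 = 0.0167 (critical value 2.394): Φ(2.83 − 2.394) = 66.8%, or 65.6% by the t-test.
- At least one of three at 0.0167: 1 − (1 − 0.668)³ = 96%.

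For r above 0 the figures come from simulating trivariate normal test statistics (1,000,000 draws):

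| r (assumed) | Any of three at 0.05: familywise error | All three at 0.05: power | Bonferroni or Holm: power for at least one | Holm: power per measure |
|---|---|---|---|---|
| 0 | 14.3% | 53% | 96% | about 76% |
| 0.5 | 12.5% | 62% | 88% | about 75% |
| 0.7 | 10.9% | 67% | 83% | about 74% |
| 0.8 | 9.8% | 70% | 80% | about 73% |
| 0.9 | 8.4% | 73% | 76% | about 72% |

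The error column counts significance in either direction. The all-three rule and Bonferroni or Holm keep the error at or below 5%.

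**Step 3: what 80% would need.** For all three at 0.05, about 94, 87, 83 and 75 evaluable per arm at r = 0, 0.5, 0.7 and 0.9. Divided by 0.59, that is 160, 148, 141 and 128 recruited per arm, against the planned 109. For 80% on each measure at 0.0167, 86 evaluable and 146 recruited per arm (292 in total).

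**Step 4: a fixed test order.** Testing one named measure at 0.05, and each later one at 0.05 only if the previous test is significant, holds the overall error at 5%. It keeps 80% power for the first measure with the planned 109 per arm. The power to reach significance on all three is then the all-three column above.

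**The case against.** The strongest reply is that a multiplicity procedure is commonly left to the analysis plan, which is not shown, and that this is a condensed article. That has force. It cannot be said that the trial has no rule or that no adjustment will be made, only that the article states none. It does not remove the point, because the primary set and its alpha and power are fixed in this document. The Outcome measures section also sends the reader to Statistical methods for aggregation, where no rule for combining the measures appears. Whatever an unseen plan says, the Sample size section would still have to say which measure or rule its figures describe.

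A second reply is that several primaries were chosen for a reason, complex trauma, and that the hypothesis names all three domains. This stands. Choosing one lead measure is a judgement, and keeping the three co-equal is legitimate if the power is restated.

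A third is that the calculation uses an unadjusted comparison while linear mixed models are planned. These may gain precision from baseline data, so the power figures are approximate.

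A reader might also infer that d = 0.5 is less secure for PHQ-9 and GAD-7, since entry depends only on CRIES-8. The documents do not support this. They give no standard deviation or expected effect by measure, and the Teaching Recovery Techniques section reports decreases in depression as well as PTSD symptoms.

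**Conclusion.** The point holds in this form: the stated 5% and 80% belong to one unnamed two-sided comparison and cannot both be assumed for the three-measure primary outcome until a success rule is stated. Under the two simplest readings, one of them fails: familywise error of 8.4% to 14.3% for any of three, or power of 53% to 73% for all three. These sizes rest on 64 evaluable per arm, d = 0.5 on every measure for the power figures, and assumed correlations from 0 to 0.9.

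A reader might go further and conclude that either the 5% or the 80% must be wrong. That does not follow. Both are correct for a single test. Both also hold under a fixed order, with the 80% attached to the first measure, and under Bonferroni or Holm with at least one success up to r of about 0.8. Nor can it be said without conditions that the error rate more than doubles. That requires an any-of-three claim at unadjusted 0.05, which the article does not adopt, and a correlation below about 0.78. At 0.9 the error is about 1.7 times the nominal level (8.4/5).

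**What to change.** State one success rule in Statistical methods and tie the Sample size section to it.

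- **Fixed order (for example).** Test CRIES-13 at T2 first, since its short form is the entry criterion. Then test PHQ-9 and GAD-7 in an order set in advance, each at two-sided 0.05 and only if the preceding test is significant. State that the 80% power applies to CRIES-13. The cost is that PHQ-9 and GAD-7 cannot be claimed confirmatorily if CRIES-13 fails.
- **Co-equal measures.** If the complex-trauma rationale is to keep all three level, use Holm and restate the power: about 66% per measure at the Bonferroni first step, about 72% to 76% per measure under the full Holm procedure if d = 0.5 on all three, and at least 80% for one or more successes only up to r of about 0.8. The cost is a stated power per measure below 80%.

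Either change is one of wording in the protocol and analysis plan, with a matching registry update, and needs no extra participants. The Trial status section shows recruitment still open under this version, so the rule can be set before the analysis.

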### Recruitment

Youth (males and females) will be referred to the trial by community workers (e.g. nurses, social workers, NGO staff members) who have concerns about the youth’s mental health. Youth can also self-refer. The CRIES-8 [21] will be used to identify youth with symptoms of PTSD. Those with scores ≥17 will be offered participation in the study. The Child Health and Parenting (CHAP) research group at Uppsala University has established relationships with community sites with TRT-trained staff across Sweden (e.g. Huddinge, Linköping, Uppsala, Östersund, Stockholm, Västerås). New sites will be approached during the trial period. It is anticipated that around 10 sites will recruit to the trial. Information about the study will be distributed to community sites directly by CHAP and posted online on the CHAP website. In an exploratory study, 90% of those screened for participation met the cutoff on the CRIES-8 [28]. The treatment retention rate was 59%, with most dropouts occurring right before or just after the start of the group. To take these factors into account, an over-recruitment is planned for the present project.

Youth who meet the inclusion criteria will be invited to a group ‘information and assessment’ meeting. Written informed consent and pre-intervention measures will be collected by the research team at the meeting prior to randomisation on site. The informed consent relates only to the SUPpORT study; no ancillary studies are planned. No biological specimens will be collected as part of the SUPpORT study.

If a youth is randomised to the intervention group but does not attend the TRT sessions, he/she will remain in the research study and will be contacted at the data collection points. The youth (and legal guardian if the youth is < 15 years) will be informed of his/her right to withdraw from the research study. Youth will be informed that they can withdraw at any time and do not need to give a reason, and there will be no negative outcomes from withdrawing. No further data will be collected for withdrawn cases. All existing data will be retained unless a youth/legal guardian also asks for it to be removed (youth/legal guardians will be informed that this is possible up to the point that the data is analysed). Youth will be able to receive the TRT programme regardless of whether they withdraw their involvement in the research study.

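### The planned 'moderation' analysis relates improvement status to participant characteristics without trial arm, so as worded it shows who improves, not who benefits from TRT (objective 3)

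*Protocol article*

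**What the plan says.** Objectives, third item: identify the subgroups that gain most and least from TRT.

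Statistical methods sets out four relevant steps:

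- Arms are compared by intention to treat with linear mixed models. The primary outcome is the total score on CRIES-13, PHQ-9 and GAD-7 at T2.
- For these three measures, "participants will also be classified as ‘recovered’, ‘improved’, ‘unchanged’ or ‘deteriorated’ based on the Reliable Change Index (RCI") and clinically significant change.
- "The proportions of classifications will be compared across the trial arms". This comparison is overall, not by subgroup.
- "Further moderation analyses will examine the associations between improvement status and" participant characteristics, with age, gender and suicidal ideation as examples.

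The last sentence is the only analysis that corresponds to the third objective. The Demographics questionnaire and Refugee Trauma History Checklist sections add that these T1 data will serve, among other uses, to form subgroups. They do not say how benefit will be compared between subgroups.

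**The concern.** A characteristic moderates the effect of TRT if the TRT-minus-waitlist difference changes with it. An association between improvement status and a characteristic is a different quantity: it also includes everything that makes some youth improve without TRT. Three features of this trial make the difference matter.

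- **Entry on a high score.** Participants: youth must score at least 17 on CRIES-8, so some regression to the mean is expected in both arms.
- **Status depends on the starting point.** The classification uses movement from a clinical to a non-clinical state. There is no entry threshold on PHQ-9 or GAD-7, so a youth who starts in the non-clinical range on one of these cannot make that move. Any characteristic linked to baseline severity is then linked to status in either arm.
- **Suicidal ideation overlaps with an outcome.** It is a named characteristic, but its source and time point are not given. If the ninth PHQ-9 item supplies it, the same item also contributes to the PHQ-9 score that defines improvement. PHQ-9 is collected at T1, T2 and T3, and a value taken after randomisation could itself be affected by TRT.

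At stake is the answer to one of the five objectives: a subgroup could be reported as benefiting most or least when the effect of TRT is the same in all.

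**Working it through.** **1. The plan's own figure.** Sample size gives 64 per arm for an effect of 0.5 at 80% power, inflated for 41% dropout. A two-sided two-sample t-test at 0.05 gives 63.77, so 64. Then 64/(1 − 0.41) = 64/0.59 = 108.5, so 109 per arm and 218 in total. The figure reproduces and this point does not affect it. The article gives no figure for the moderation analysis. Below, 64 per arm stands for the analysable sample and 109 for no dropout.

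**2. What each analysis estimates.** Assumed inputs, not in the documents: a binary characteristic X that splits the sample in half; improvement on the waitlist in 15% (X = 0) and 40% (X = 1); TRT adds 15 points in both groups. TRT rates are then 30% and 55%. The benefit of TRT is 15 points in each group, so there is no moderation.

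- Interaction: (0.55 − 0.30) − (0.40 − 0.15) = 0.
- Association in the TRT arm: 0.55 − 0.30 = 0.25.
- Association with arms pooled: (0.55 + 0.40)/2 − (0.30 + 0.15)/2 = 0.475 − 0.225 = 0.25.

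The association is 25 points whichever way it is taken, while the quantity asked for in the objective is zero.

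**3. How often this would be flagged, 64 per arm.**

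- TRT arm, 32 per group: SE = √(0.55×0.45/32 + 0.30×0.70/32) = 0.120; z = 0.25/0.120 = 2.09; probability of p < 0.05 about 55%.
- Pooled, 64 per group: SE = √(0.475×0.525/64 + 0.225×0.775/64) = 0.081; z = 3.07; about 87%.

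Simulation (4,000 trials) agrees:

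| Test | 64 per arm | 109 per arm |
|---|---|---|
| Association, TRT arm | 55% | 77% |
| Association, pooled | 86% | 97% |
| Arm-by-X interaction | 5% | 5% |

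A second set-up used a continuous characteristic correlated 0.3 with change equally in both arms, an arm effect of 0.5, and improvement defined as change above 0.8 (3,000 trials, 64 per arm). It gave 46% in the TRT arm, 71% pooled and 5% for the interaction on the continuous change.

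**4. Dependence on the assumption.** Take a weaker characteristic: 15% against 25% on the waitlist, hence 30% against 40% with TRT.

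- TRT arm: SE = √(0.40×0.60/32 + 0.30×0.70/32) = 0.119; z = 0.84; about 13%.
- Pooled: SE = √(0.325×0.675/64 + 0.225×0.775/64) = 0.078; z = 1.27; about 25%.

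With no prognostic value the rate falls to about 5%.

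**5. Precision of the interaction test.** Continuous outcome with SD 1, two equal subgroups, n per arm: SE = √(4/(n/2)); detectable at 80% power = (1.96 + 0.84) × SE.

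- n = 64: SE = √(4/32) = 0.354; detectable 0.99 SD; power for 0.5 SD is Φ(0.5/0.354 − 1.96) = 29%.
- n = 109: SE = √(4/54.5) = 0.271; detectable 0.76 SD; power for 0.5 SD is 45%.
- Gender, if the 86% share of boys quoted in Background for 2015 arrivals applied here: SE = √(2/(0.86n) + 2/(0.14n)); detectable 1.43 SD (n = 64) or 1.09 SD (n = 109).

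**The case against.** **The label may carry the meaning.** The article calls these moderation analyses, and the surrounding text concerns the intervention effect and comparison across arms. The sentence may be a compressed description of an interaction model, with detail left to an analysis plan not shown. This has weight: a reader should not infer that the trial team has chosen a model without arm, nor that the association would be run in one particular sample. But the article goes beyond the label. It states which two quantities will be associated, arm is not one of them, and nothing elsewhere corrects it. That is a stated analysis that misses its objective, not an omitted detail.

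**The dose analysis.** A reader might extend the criticism to the plan to "quantify the extent to which the intervention effect on the primary outcomes is determined by participation in the intervention (number of sessions received"), since attendance is self-selected and in the exploratory study "The treatment retention rate was 59%, with most dropouts occurring right before or just after the start of the group". The documents do not support that. The sentence is about the intervention effect, names no estimator, and belongs with fidelity, where "Session attendance lists will also be shared with CHAP to inform individual participant dose". It is not offered as the answer to the third objective. A naive regression of outcome on sessions within the TRT arm would be open to bias, but the article does not say that this is planned. Nor is a complier-average effect with randomisation as the single instrument an obvious replacement: it mainly rescales the intention-to-treat effect and does not show whether more sessions give more benefit.

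**The outcome class.** Using improvement categories is not in itself an error. An arm-by-characteristic test can be run on them, and the primary outcome remains the continuous score.

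**Consequences.** A reader might infer that subgroup results would decide who is offered TRT in stepped care. The article says only that a stepped-care model needs developing.

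**Conclusion.** The point holds for the moderation analysis. As worded, it measures who improves and cannot separate that from who benefits from TRT, so it does not answer the third objective. The direction follows from the definition; the size depends on how prognostic the characteristic is, which the documents do not give. Under the two moderately strong assumptions used, with no true moderation and 64 per arm, a false subgroup signal appears in about half of trials within the TRT arm and in 71% to 86% with arms pooled, against about 5% for the interaction. With a weaker characteristic the rates are about 13% and 25%. The point should be settled before analysis. It does not touch the primary comparison or the sample size.

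**What to change.** Replace the sentence with, for example: 'Moderation will be examined by arm-by-characteristic interactions in the linear mixed models for the continuous T2 total scores, using both trial arms and characteristics measured at T1 (including suicidal ideation). Interaction estimates will be reported with 95% confidence intervals and labelled exploratory.' Name the T1 characteristics and the source of the suicidal-ideation variable. The improvement-status version may stay as a supplement if it also includes the arm interaction.

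The cost is a change of wording and modest analysis work. The T1 characteristics, both arms, the T2 scores and the mixed model are already planned. The downside is wide intervals: only interactions of roughly 0.76 to 0.99 SD are detectable with equal subgroups, and larger ones still are needed for an uneven split such as gender. The report should say so, and should not read a non-significant interaction as evidence of equal benefit.
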